# A multimodal precision-prevention approach combining lifestyle intervention with metformin repurposing to prevent cognitive impairment and disability: the MET-FINGER randomised controlled trial protocol

**DOI:** 10.1186/s13195-023-01355-x

**Published:** 2024-01-31

**Keywords:** Alzheimer’s, Dementia prevention, Cognitive impairment, Lifestyle-drug combination therapy, Lifestyle intervention, Metformin, World-Wide FINGERS, Drug repurposing, *APOE*

## Abstract

**Background:**

Combining multimodal lifestyle interventions and disease-modifying drugs (novel or repurposed) could provide novel precision approaches to prevent cognitive impairment. Metformin is a promising candidate in view of the well-established link between type 2 diabetes (T2D) and Alzheimer’s Disease and emerging evidence of its potential neuro-protective effects (e.g. vascular, metabolic, anti-senescence).

MET-FINGER aims to test a FINGER 2.0 multimodal intervention, combining an updated FINGER multidomain lifestyle intervention with metformin, where appropriate, in an *APOE* ε4-enriched population of older adults (60–79 years) at increased risk of dementia.

**Methods:**

MET-FINGER is an international randomised, controlled, parallel-group, phase-IIb proof-of-concept clinical trial, where metformin is included through a trial-within-trial design. 600 participants will be recruited at three sites (UK, Finland, Sweden). Participants at increased risk of dementia based on vascular risk factors and cognitive screening, will be first randomised to the FINGER 2.0 intervention (lifestyle + metformin if eligible; active arm) or to receive regular health advice (control arm). Participants allocated to the FINGER 2.0 intervention group at risk indicators of T2D will be additionally randomised to receive metformin (2000 mg/day or 1000 mg/day) or placebo. The study duration is 2 years. The changes in global cognition (primary outcome, using a Neuropsychological Test Battery), memory, executive function, and processing speed cognitive domains; functional status; lifestyle, vascular, metabolic, and other dementia-related risk factors (secondary outcomes), will be compared between the FINGER 2.0 intervention and the control arm. The feasibility, potential interaction (between-groups differences in healthy lifestyle changes), and disease-modifying effects of the lifestyle-metformin combination will be exploratory outcomes.

The lifestyle intervention is adapted from the original FINGER trial (diet, physical activity, cognitive training, monitoring of cardiovascular/metabolic risk factors, social interaction) to be consistently delivered in three countries. Metformin is administered as Glucophage®XR/SR 500, (500 mg oral tablets). The metformin/placebo treatment will be double blinded.

**Conclusion:**

MET-FINGER is the first trial combining a multimodal lifestyle intervention with a putative repurposed disease-modifying drug for cognitive impairment prevention. Although preliminary, its findings will provide crucial information for innovative precision prevention strategies and form the basis for a larger phase-III trial design and future research in this field.

**Trial registration:**

ClinicalTrials.gov (NCT05109169).

**Supplementary Information:**

The online version contains supplementary material available at 10.1186/s13195-023-01355-x.

## Background

The long preclinical stages of Alzheimer’s disease (AD) preceding cognitive impairment and subsequent dementia provide opportunities for prevention [1]. Despite recent promising findings from anti-amyloid monoclonal antibodies, [2–4] the failure of many single-intervention pharmacological and non-pharmacological trials in AD highlights an urgent need for new multimodal therapy approaches targeting simultaneously several disease mechanisms and modifiable risk factors [5, 6]. AD is a heterogeneous disease, and targeting a single pathology, e.g. amyloid, may not be sufficient to impact disease development and progression to reduce dementia risk [7–9]. The complex pathological processes leading to dementia unfold on multiple levels, e.g. shared risk factors, interaction of different pathology mechanisms, and synergistic effects on cognition. Nonetheless, although multimodal interventions have started to be considered for AD/dementia, only the result of few studies is available to date.

The key challenges in implementing the right interventions for the right people at the right time, and defining accessible and sustainable strategies worldwide, are also clearly emphasized in the recent World Health Organization Guidelines for Risk Reduction of Cognitive Decline and Dementia [10, 11]. Combinations of lifestyle (including multidomain) and pharmacological interventions have been successfully tested in at-risk individuals for the prevention of cardiovascular disease (CVD) [12] and type 2 diabetes (T2D), [13, 14] which share many modifiable risk factors, [15] and potential underlying mechanisms with dementia [9]. Precision approaches combining multimodal lifestyle intervention with repurposed putative disease-modifying-drug could provide effective strategies for dementia prevention or risk reduction.

So far, the multimodal lifestyle-based Finnish Geriatric Intervention Study to Prevent Cognitive Impairment and Disability (FINGER, ClinicalTrials.gov — NCT01041989) [16] is the only intervention model that showed significant cognitive benefits in cognitively normal at-risk older adults and is now being adapted and tested within the World-Wide FINGERS global network of multimodal dementia prevention trials (to date, 45 + member countries) [17]. Additionally, unhealthy lifestyle habits, T2D, insulin resistance, and increased adiposity (overweight/obesity) have been consistently linked to the risk of dementia/AD through several mechanisms which could be targeted by metformin, the recommended first-line treatment in adults with T2D (Fig. 1) [18–20]. Biological mechanisms of ageing may also play a role in neurodegenerative disorders, and increasing evidence supports a potential role of metformin in counteracting such mechanisms [21]. Furthermore, it has been proposed that the development of novel AD therapeutics could be framed in the context of biological gerontology [22]. This suggests that pharmacologic strategies for decreasing insulin resistance and preventing T2D may also help reduce the risk of cognitive impairment with metformin as a promising candidate for a combined lifestyle-drug intervention to prevent or delay cognitive impairment.

**Fig. 1 Fig1:**
[figure not shown]
Summary of the mechanisms linking type 2 diabetes (T2D) and its risk factors to dementia/AD and possible metformin targets (Modified from Yarchoan M and Arnold SE, Diabetes, 2014)

The MET-FINGER study aims to test a FINGER 2.0 multimodal intervention (active arm), combining a Structured Multimodal Lifestyle Intervention (SMLI, based on the original FINGER model) with metformin (where appropriate) in a *APOE* ε4-enriched population of older adults at-risk for dementia, against a Self-Guided Multimodal Intervention (SGMI, general health advice; control arm).

The primary objective is to test the effect of the FINGER 2.0 intervention versus the SGMI on change in global cognition. Secondary objectives are to test the effect of the FINGER 2.0 intervention versus the SGMI on change in individual cognitive domains, functional status, and lifestyle, vascular, metabolic and other dementia-related risk factors. Exploratory objectives will investigate, within the SMLI-metformin combination groups, (i) potential interactions between metformin and lifestyle changes; (ii) potential disease-modifying effects of the lifestyle-metformin combination; and (iii) feasibility of the metformin + lifestyle combination; in the context of prevention of cognitive impairment.

## Methods

### Study design

MET-FINGER is a randomised, controlled, parallel-group, multicentre phase-IIb proof-of-concept clinical trial testing the FINGER 2.0 multimodal lifestyle-based intervention, including a pharmacological trial-within-trial with metformin (Fig. 2). The participants will be first randomised 1:1 to the FINGER 2.0 intervention (SMLI for all participants + metformin where appropriate; active arm) or the SGMI (regular health advice; control arm). Participants allocated to the FINGER 2.0 intervention, and with indicators T2D risk, but no diagnosed/suspected diabetes, will be randomised 1:1:1 to receive metformin 2000 mg/day, metformin 1000 mg/day, or placebo, together with the SMLI. Participants allocated to the FINGER 2.0 intervention but not eligible for metformin treatment will receive the SMLI alone. At each site, both randomisation steps (Fig. 2) are carried out using a computer-generated list from the OpenClinica database. In each randomisation step, the list is stratified by site and programmed using random blocks of various sizes.

**Fig. 2 Fig2:**
[figure not shown]
Diagram of the MET-FINGER trial. The main trial comparison is between the FINGER 2.0 Multimodal (combining a Structured Multimodal Lifestyle Intervention (SMLI) and metformin, where appropriate) vs the Self-Guided Multimodal intervention (SGMI). Metformin treatment is included in the FINGER 2.0 Multimodal Intervention through a trial-within-trial where participants who are eligible for metformin treatment will be randomly allocated to one of the three metformin/placebo treatments in addition to the SMLI. Ineligible participants for the metformin treatment will continue participation receiving the SMLI alone. The study, therefore, includes two screening and randomisation steps. The first screening step will assess eligibility for full study participation and eligible participants will be equally randomised to either the FINGER 2.0 or the SGMI. The second screening step will determine specific eligibility to the metformin treatment and eligible participants will be randomised as described above

The metformin/placebo allocation and treatment will be double-blinded. Primary outcome assessors will be blinded to the FINGER 2.0 versus control allocation, and they will not be involved in the lifestyle intervention.

### Participants

Six hundred participants will be included across three sites to obtain an *APOE* ε4-enriched population (≥ 50%).

In the United Kingdom (UK), participants (*n* ~ 300) will be recruited at Imperial College London (ICL) from the Cognitive Health in Ageing Register: Investigational, Observational and Trial studies (CHARIOT). In Finland, participants (*n* ~ 200) will be recruited via the Finnish Institute for Health and Welfare (THL) biobank. In Sweden, participants (n ~ 100) will be recruited from the electronic database and biobank for clinical dementia research at Karolinska University Hospital (KUH) Theme Inflammation and Aging, Theme medical unit (GEDOC).

Within the relevant registries, potential participants will be first invited for Screening for Lifestyle (Fig. 2) based on age and other eligibility criteria, depending on data availability. Eligible participants will be further invited to participate in the full study. At all sites, participants for whom *APOE*-genotype data is available will be invited for screening starting with an approximate 50/50 ε4 carrier/non-carrier ratio. Carriers have at least one ε4-allele. To ensure 50% minimum enrichment in the overall trial cohort and a similar carrier/non-carrier ratio at all sites, carrier/non-carrier ratio within the eligible population is regularly monitored to adjust the proportion of ε4 carrier/non-carrier invited. The site-stratified randomisation ensures a similar carrier/non-carrier ratio in the two groups at all sites. If needed, participants may be newly genotyped. At Screening for Lifestyle, participants can request disclosure of their APOE genotype. Other recruitment sources (e.g. media campaign) may be used if needed to reach the recruitment target.

Two separate sets of eligibility criteria will be applied within the study (Table 1). The Study Eligibility Criteria aim to identify older adults with some indicators of modifiable risk factors for dementia and cognitive performance at the mean level or slightly lower than expected for age according to population norms, but no substantial cognitive impairment nor conditions preventing safe and effective engagement in the SMLI. The Metformin Eligibility Criteria aim to identify participants with indicators of increased T2D risk, no diagnosed/suspected diabetes and no metformin contraindications. The metformin/treatment will be initiated in all participants who will meet the Metformin Eligibility Criteria (Table 1) and successfully undergo additional metformin-specific safety assessments (e.g. electrocardiography, vitamin B12 blood levels).

**Table 1 Tab1:** Eligibility criteria

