### Statistics

The trial primary comparison is Self-Guided versus FINGER 2.0 multimodal intervention arm, and the trial has been powered for this purpose. Power calculations for the primary outcome are based on FINGER data. FINGER included 1260 participants (~ 33% *APOE* ε4 carriers), with an overall drop-out rate of 12% during the 2-year intervention. We estimate that a smaller sample size would be sufficient for MET-FINGER, based on (i) *APOE* ε4 enrichment at least 50% (stratified analysis of FINGER data indicated intervention benefits especially among ε4 carriers); [25] (ii) potential added benefit of metformin; and (iii) optimization of the initial FINGER lifestyle intervention. In FINGER, the observed mean 2-year change (SD) in primary outcome among *APOE* ε4 carriers was 0.10 (0.38) in the control group, and 0.19 (0.34) in the intervention group. A sample size of 506 participants would be needed to demonstrate a between-group difference with 80% power and at 5% significance level. Assuming a 15% drop-out over 2 years, a total sample size of 600 participants would be required.

The primary efficacy analysis will be based on the modified intention-to-treat population, including all randomly assigned participants with baseline and at least one post-baseline observation.

Appropriate transformation to skewed NTB components will be applied. Mixed-effects regression models with maximum likelihood estimation will be applied to analyse change in cognitive scores, as a function of randomization group, time, and group × time interaction. The site will also be included in the model as fixed effect. Non-linearity of change will be taken to account. The other secondary endpoints will be analysed using the appropriate generalised mixed-effects regression model depending on the outcome distribution.

Potential heterogeneity of intervention effects will also be investigated in subgroup analyses, for both primary and secondary outcomes by, e.g. demographics, *APOE* ε4 carrier status, baseline cognitive and functional level, and intervention adherence, although the trial is not powered for such analyses.

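### Site-stratified randomisation does not ensure a similar APOE ε4 carrier ratio in the two arms at every site; it gives that balance only in expectation

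*Protocol article*

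**What the plan says.** On balance between arms, the Participants section says: "The site-stratified randomisation ensures a similar carrier/non-carrier ratio in the two groups at all sites". The same section describes how the carrier share is controlled during recruitment. Genotyped registrants are invited in a roughly even carrier/non-carrier mix, and the "carrier/non-carrier ratio within the eligible population is regularly monitored to adjust the proportion of ε4 carrier/non-carrier invited".

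The Study design section sets out the allocation: "The participants will be first randomised 1:1 to the FINGER 2.0 intervention" or the control arm, and "In each randomisation step, the list is stratified by site and programmed using random blocks of various sizes". No factor other than site is named.

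The Statistics section gives the primary model as a mixed-effects regression on randomisation group, time and their interaction, and adds: "The site will also be included in the model as fixed effect". APOE ε4 status appears there in two other roles. It is part of the sample size rationale, which uses 2-year changes observed in ε4 carriers of the earlier FINGER trial, and it is one of the subgroup factors, for which the article says the trial is not powered.

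**The concern.** Stratification with blocking constrains only the factors that define the strata. Here that is site, so arm sizes are held close within each site. Carrier status lies outside the strata and is balanced on average over repeated randomisations, not in the one that is carried out. The recruitment measures do not close the gap: they steer the carrier share of the cohort and of each site, not how carriers divide between the arms.

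The sentence matters because APOE is not an incidental covariate in this trial. It is the enrichment factor, the sample size rests on carrier data, and the article expects more benefit in carriers. A reader or analyst who takes balance as guaranteed by design could conclude that adjustment is unnecessary and that checking carrier share by arm and site is superfluous.

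**Working it through.** **Inputs.** Site sizes from the Participants section: about 300 in the UK ("In the United Kingdom (UK), participants (*n* ~ 300) will be recruited"), 200 in Finland ("In Finland, participants (*n* ~ 200) will be recruited") and 100 in Sweden ("In Sweden, participants (n ~ 100) will be recruited"). Allocation is 1:1. Carrier share is assumed to be 50%, the article's minimum. From the Statistics section: mean change (SD) 0.10 (0.38) in control and 0.19 (0.34) in intervention, 80% power, 5% significance, 15% drop-out.

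**The plan's own figure.** Difference = 0.19 − 0.10 = 0.09. Pooled SD = √((0.38² + 0.34²)/2) = 0.3606. A two-sided t-test needs 253 per arm, so 506, as stated. 506/0.85 gives 596, rounded up to 600. The figure reproduces, and nothing below changes it.

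**Carrier balance under site-only strata.** If N participants at a site are split equally without regard to genotype, the number of carriers in one arm is hypergeometric. With carrier share p, the between-arm difference in carrier share has SD = √(4p(1−p)/(N−1)). At p = 0.5 this is 1/√(N−1). The 95% range is ±1.96 × SD; the tail probabilities are exact.

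| | N | SD (points) | 95% range (points) | Chance of ≥10 points |
|---|---|---|---|---|
| UK | 300 | 5.8 | ±11.3 | 8% |
| Finland | 200 | 7.1 | ±13.9 | 20% |
| Sweden | 100 | 10.0 | ±19.7 | 32% |
| Whole trial | 600 | 4.1 | ±8.0 | 1.8% |

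In Finland an exact 10-point difference is possible, so the cut-off matters: the chance of more than 10 points is 12%, against 20% for at least 10. For the whole trial, the chance of more than 10 points is 1.1%.

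Chance that at least one site differs by 10 points or more: 1 − (1 − 0.083)(1 − 0.203)(1 − 0.317) = 0.50. For 15 points or more, the site probabilities are 0.8%, 3.4% and 16.1%, which gives 20%. With 60% carriers the results barely change (Sweden ±19.3 points, 31%).

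**Consequence for the primary estimate.** The shift in the group difference is roughly the imbalance multiplied by the carrier versus non-carrier difference in 2-year change. The article does not give the latter, so a range is assumed. At an 8-point imbalance:

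- 0.05: 0.08 × 0.05 = 0.004, or 4% of 0.09
- 0.10: 0.08 × 0.10 = 0.008, or 9%
- 0.20: 0.08 × 0.20 = 0.016, or 18%

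The standard error implied by the sample size inputs is 0.3606 × √(2/253) = 0.032, so these shifts are about 0.1 to 0.5 standard errors.

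**The case against.** The strongest reply is that this is a matter of one word. Not stratifying by APOE is a legitimate choice. Chance imbalance in a baseline factor does not bias a randomised comparison or raise the type I error, and the usual standard error already allows for it. The primary analysis pools the sites, so the relevant imbalance is the trial-wide ±8 points and not Sweden's ±20. All of this stands, and it limits how serious the point is. It does not make the sentence true, since the claim is made for all sites.

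Three stronger readings are tempting, and the article does not support them.

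- **That no adjustment for APOE is planned.** The Statistics section lists group, time, their interaction and site, but does not say that the list is complete. Covariates are commonly left to the analysis plan, which is not shown and may include APOE.
- **That the randomisation list should simply have used APOE.** Monitoring of the carrier ratio among eligible people suggests that most genotypes are known before the first randomisation. The article also allows new genotyping where needed and other recruitment sources such as media campaigns, so it does not establish this for every participant.
- **That the same fault affects the metformin/placebo randomisation or undermines the carrier subgroup analyses.** The sentence concerns the two main groups only and makes no claim about the three drug arms, whose outcomes are exploratory. Comparisons within carriers remain randomised comparisons, and a 45/55 split keeps 4 × 0.45 × 0.55 = 99% of the efficiency of an even one.

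**Conclusion.** The statement is wrong as written: with site as the only stratum, carrier status is balanced between arms in expectation only. At the level for which the claim is made, the departure is material, since the chance that some site differs by 10 points or more is about even. At the level of the primary estimate the effect is likely to be small, at most about half a standard error for an imbalance at the edge of the 95% range, and there is no bias. The site figures assume about 50% carriers and the planned site sizes, and are insensitive to a carrier share of 60%. The figures for the estimate rest on an assumed 0.05 to 0.20 difference in change between carriers and non-carriers. The point calls for a corrected statement and a prespecified covariate; it is not evidence that the primary comparison is invalid.

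**What to change.** 1. Replace *ensures* with *is expected to give* in the Participants section, and plan to report carrier share by arm and site. This costs one sentence and one table row.
2. Prespecify APOE ε4 carrier status and its interaction with time as covariates in the primary mixed model, unless the analysis plan already does so. This costs a few extra parameters. The article puts the primary analysis at September 2029, so on that timetable there is time to do it beforehand.
3. Optionally, stratify the first randomisation by site and carrier status (six strata), only for participants not yet randomised whose genotype is known beforehand. Enrolment was estimated to finish in February 2025, so few or none may remain. Block sizes are not stated. If sizes of 4 to 8 are assumed and the scheme were applied throughout, the largest possible difference at full site size would be about 1.3 to 2.7 points in the UK, 2 to 4 in Finland and 4 to 8 in Sweden. The cost is an amended list in the randomisation system.

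The sample size of 506, inflated to 600, stays as it is.

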**Study eligibility criteria**
*Inclusion criteria*
1. Age 60–79 years
2. CAIDE Dementia Risk Score ≥ 6 points
3. Cognitive performance at the mean level or slightly lower than expected for age according to local population norms based on the MoCA test and the CERAD verbal learning test. This criterion is met if at least one of the following conditions is met:
a) MoCA score ≤ 25 AND ≥ 15^a^
b) CERAD immediate recall score ≤ 19
c) CERAD delayed recall score ≤ 75% of the last immediate recall attempt
4. Proficiency in the local language (English, Finnish or Swedish)
*Exclusion criteria*^b^
1. Dementia or substantial cognitive impairment (e.g. memory clinic referral needed as judged by the study physician)
2. Current or past use of medications for AD or related diseases (e.g. cholinesterase inhibitors, memantine)
3. Diminished decision-making capacity, not capable of consenting or completing study assessments, based on clinical judgement
4. Other known significant neurologic diseases (including, e.g. Parkinson’s disease, Huntington’s disease, normal pressure hydrocephalus, brain tumour, progressive, supranuclear palsy, seizure disorder, subdural haematoma, multiple sclerosis, or history of significant head trauma with persistent neurologic sequelae or known structural brain abnormalities)
5. Any other condition affecting safe engagement in the intervention (e.g. malignant disease, major depression, symptomatic cardiovascular disease, revascularisation within the previous year)
6. Severe loss of vision, hearing, or communicative ability; conditions preventing cooperation
7. Coincident participation in the active phase of another intervention trial
8. A member of the household already enrolled in the MET-FINGER trial
